## 5. Conclusions

The RASDOP study will determine whether the inclusion of radiofrequency in a multimodal physiotherapy treatment—based on PFMT, therapeutic education, and the management of MPS in the abdominal and PFM—enhances its effectiveness in relieving pain and improving sexual function in postpartum women. Additionally, it will explore the barriers and facilitators that influence postpartum women’s adherence to conservative treatment and home-based recommendations for alleviating pelvic pain.

## Figures and Tables

**Figure 1 jcm-14-01489-f001:**
[figure not shown]
CONSORT follow Diagram. FPSM-RG: Physiotherapy in Women’s Health Research Group, A: assessment; IC: informed consent; MP-G: multimodal physiotherapy group; RMP-G: radiofrequency + multimodal physiotherapy group; PFMT: pelvic floor muscle training.

**Table 3 jcm-14-01489-t003:** Proposed interview guide for the RASDOP study.

Number	Questions
1.	What has been your experience participating in this physiotherapy program?
2.	What motivated you to participate in this physiotherapy program? What were your goals or objectives? What did you aim to achieve? Do you think you have achieved them?
3.	From your perspective, what aspects have made it difficult to achieve the goals or objectives of this program? How could we have supported you better?
4.	Was it easy or difficult for you to attend the treatment and evaluation sessions? Why? Have we made it easier for you in any way? Is there anything that could have made it even easier?
5.	Have you been able to apply the knowledge gained during the treatment or evaluation sessions? What facilitated this? What made it more difficult?
6.	Have you adopted or modified any habits that you believe have improved your pelvic health? What about other aspects of your general health? Which ones? Was it easy to adopt these habits? Why? Was it difficult? Why?
7.	Do you believe that attending pelvic floor physiotherapy has been important for your recovery? Why? Do you think you would have needed any other treatments, guidance, advice, or modifications to the program? Are there any treatments, guidance, or advice that you consider unnecessary?
8.	What were and are your expectations regarding the improvement in pelvic pain? Do you think you have done or are doing anything to help alleviate it? Do you feel that you need or would have needed anything else?
9.	Do you think there is anything more or different we could do to help women experiencing pelvic and/or perineal pain postpartum?

The first question from each numbered set will be asked. Follow-up questions will be posed as needed based on the flow of the interview.

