#### 2.3.1. Research Teams and Reflexibility

The individual interviews and focus groups will be conducted by two physiotherapists specialized in Pelvic and Women’s Health, who are women, mothers, university professors, and hold a PhD. Interviewer 1 (PT1) will be familiar with the participants in advance, as she is the blinded evaluator of the RCT. This evaluator will interview the women who have already completed the follow-up in order to avoid conflicts related to the potential disclosure of the intervention group during the interviews. Interviewer 2 (PT2) will not know the participants in advance and will conduct interviews with women who are between the A2 and A4 follow-up assessments. Both evaluators have prior experience conducting individual interviews and focus groups within the framework of qualitative studies in women’s health.

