#### 2.3.2. Qualitative Study Design

The theoretical framework and methodological orientation for the qualitative part of the RASDOP study is based on phenomenology. The main objective will be to understand the experience of postpartum women in adhering to a physiotherapy treatment aimed at improving their postpartum pelvic pain.

Women who have completed the 12 individual physiotherapy sessions will be included, regardless of the assigned treatment group of the RCT. Women will be divided into two groups: one consisting of women who are in the follow-up period (3 to 12 months after completing the intervention), or those who have already finished their participation in the study (> 12 months after the physiotherapy intervention). The recruitment will be consecutive, and the study will end when data saturation is reached. Data saturation will be deemed achieved when the information gathered aligns with that from earlier interviews.

All interviews will be conducted face-to-face and will take place in a classroom in the Nursing and Physiotherapy Building at the University of Alcalá, near the FPSM Research Group laboratory. The focus groups will consist of four to six women who do not know each other beforehand. In the interviews, only the participating postpartum women and one of the interviewers (PT1 or PT2) will be present. The interviewers will use a pre-designed question guide (Table 3), and the sessions will be audio-recorded with the prior consent of the participants.

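### Two of the nine guaranteed interview questions (set 7 clearly, set 6 mildly) are closed and worded towards benefit, and the probes that would balance set 7 are optional

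*Protocol article*

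**What the plan says.** Section 2.3.2 states that "The interviewers will use a pre-designed question guide (Table 3)", and the footnote to Table 3 gives the rule for using it: "The first question from each numbered set will be asked. Follow-up questions will be posed as needed based on the flow of the interview". Of the nine sets, therefore, only the nine lead questions are certain to reach every woman.

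Two lead questions matter here:

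- Set 6: "Have you adopted or modified any habits that you believe have improved your pelvic health"
- Set 7: "Do you believe that attending pelvic floor physiotherapy has been important for your recovery"

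In set 7, the request for reasons and the question about unnecessary treatment, guidance or advice come after the lead question, so they are asked only if the interviewer sees a need.

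Section 2.3.2 gives the main qualitative objective as "to understand the experience of postpartum women in adhering to a physiotherapy treatment aimed at improving their postpartum pelvic pain". The Introduction adds that the factors behind both adherence and non-adherence will be explored, and the Abstract speaks of barriers and facilitators.

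**The concern.** In a semi-structured interview the guaranteed questions are the part of the data collection that is the same for every woman. A guaranteed question that is closed and suggests its own answer tends to draw agreement. What a woman was never asked cannot be recovered when the transcripts are coded.

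The stake is the coverage of the adherence question. Someone who tried a recommended exercise and gave it up, or kept it up without noticing any effect, is a key informant on non-adherence. Set 6 does not ask her about that exercise, and set 7 asks her to confirm that physiotherapy mattered to a recovery she may not feel she has had.

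Two features of the design make neutral wording more valuable. Section 2.3.2 admits only women who completed all 12 sessions, so the sample already leans towards those who stayed with treatment. Interviews are also face to face with physiotherapists of the study team, and section 2.3.1 says of one of them that "Interviewer 1 (PT1) will be familiar with the participants in advance", because she is the trial's blinded assessor.

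**Working it through.** No formula applies. The check is a count of the nine lead questions in Table 3, classed by grammatical form and by the direction of the wording.

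| Set | Topic of the guaranteed question | Form | Direction |
|---|---|---|---|
| 1 | Overall experience | Open | Neutral |
| 2 | Motive for joining | Open | Neutral on benefit |
| 3 | Obstacles to reaching goals | Open | Presupposes difficulty |
| 4 | Ease of attending | Closed (either/or) | Balanced |
| 5 | Use made of what was taught | Closed (yes/no) | Presupposes knowledge gained, not symptom benefit |
| 6 | Habits credited with improvement | Closed (yes/no) | Towards benefit, mildly |
| 7 | Importance of physiotherapy for recovery | Closed (yes/no) | Towards benefit, clearly |
| 8 | Expectations about pain improvement | Open | Mentions improvement but asks about expectations |
| 9 | Anything more or different to offer | Closed in form | Invites shortcomings |

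Results:

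- Closed in form: sets 4, 5, 6, 7 and 9, so 5 of 9.
- Closed and worded towards benefit: sets 6 and 7, so 2 of 9.
- Worded towards benefit in any form: 2 of 9, or 3 of 9 if the mention of improvement in set 8 is counted.
- Neutral, balanced or inviting difficulty: sets 1, 2, 3, 4 and 9, so at least 5 of 9. Sets 5 and 8 are the remaining two (5 + 2 + 2 = 9).

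Next, what the guide can still reach in the two affected sets:

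- **Set 7.** Both written counterweights are follow-ups. A woman who answers yes need not be asked why, or whether any part of the programme was unnecessary.
- **Set 6.** The written follow-ups ask which habits were adopted and whether adopting those habits was easy or hard. They refer back to the habits named in reply to the lead question. Even if all are used, they do not ask about a recommended habit that was dropped or that made no difference.
- **Elsewhere.** Set 3 guarantees an open question about difficulty, but in reaching goals rather than in keeping up particular exercises. Set 5 could draw a no from a woman who did not use what she was taught, but its probes on what helped or hindered are also optional. No guaranteed question asks directly about recommended habits or exercises that were stopped.

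**The case against.** The strongest reply is that a guide must be judged whole. A reader might infer, from five closed lead questions out of nine, that women are steered to agree that the physiotherapy helped. The document does not support that. Closed is not the same as leading: set 4 offers both answers, set 5 asks about applying knowledge, and set 9 invites criticism. Set 1 opens with "What has been your experience participating in this physiotherapy program", which is fully neutral, and set 3 presupposes difficulty. Both are guaranteed.

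A reader might also infer that the questions come from the women's own therapists. Section 2.2.5 assigns treatment to PT3 and PT4. The interviewers are PT1, the blinded assessor, who interviews only women who have finished follow-up, and PT2, who has no part in assessment or treatment and is described in section 2.3.1 as not knowing the women beforehand. PT4 does join the transcription team (section 2.3.3), but does not ask the questions.

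Both interviewers have experience with this method, follow-ups are allowed whenever needed, and a bare yes is the natural cue to ask why. Some of the data come from focus groups of four to six women, where a one-word answer is less likely to close a topic. Set 6 asks whether any such habits exist, so no is an easy answer. The qualitative aim is adherence, not efficacy, and Table 3 is headed as a proposed guide.

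All of this stands, and it confines the point to sets 6 and 7. It does not remove it: the direction of the set 7 wording is plain, its balancing probes depend on the interviewer's discretion, and set 6 leaves a gap that its own follow-ups do not fill.

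**Conclusion.** The point holds for two of nine guaranteed questions. Set 7 is closed, presupposes recovery and points towards benefit, with its counterweights optional. Set 6 is a milder case whose main fault is coverage: habits or exercises stopped, or kept without benefit, are not asked about. Both sit awkwardly with an aim that includes non-adherence.

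The guide as a whole is not shown to steer women, and this write-up makes no such claim. No effect estimate from the randomised comparison is touched. How far answers would shift cannot be derived from the document. The conclusion assumes that the footnote is applied as written, and it rests on a reading of question wording, where set 7 is clear and set 6 is a matter of degree. This is a minor improvement to the qualitative component.

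**What to change.** Before interviewing starts, make the lead questions of sets 6 and 7 open and neutral. For example:

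- Set 6: *Which recommended habits or exercises did you try, keep or stop, and why?*
- Set 7: *What part, if any, has physiotherapy played in how you are now?*

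In set 7, make the request for reasons and the question about unnecessary treatment or advice standard rather than discretionary, and amend the footnote to say so.

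Sets 4, 5 and 9 need no change. Rewording them would be a matter of preference, and a set 9 question asking what should be done differently would presuppose fault and be more leading than the present one.

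The change is confined to Table 3 and its footnote. It needs no extra staff, visits or data, and its only cost is slightly longer interviews.

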## Data Availability

The original contributions presented in this study are included in the article; further inquiries can be directed to the corresponding author.
